#### Exclusion criteria

Exclusion criteria for METRIC (and so carried forward) are as follows:

Any psychiatric or other disorder likely to impact on informed consent.Evidence of severe comorbidities which makes it undesirable for the patient to participate in the study.Pregnancy.Contraindication to MRI (eg, cardiac pacemaker, severe claustrophobia and inability to lie flat).Final diagnosis other than CD.Enrolled in the METRIC study but not part of the final new diagnosis cohort.

### MRI

#### Sequences

METRIC recruits underwent a standard minimum MRE sequence data set (1.5 T or 3 T) (table 1). This will also be required for retrospective accruals, excepting diffusion-weighted imaging (DWI) which is unnecessary to calculate relevant activity and bowel damage indices.

**Table 1 T1:** Required and optional sequences for the magnetic resonance enterography studies

Required	Optional
Coronal TrueFISP	Axial TrueFISP
Axial HASTE	Dynamic TrueFISP motility
Coronal HASTE	
Coronal HASTE with fat suppression	Axial HASTE with fat suppression
Axial DWI (b50 and b600)*	Additional b values
Coronal pregadolinium and postgadolinium VIBE (60–70s)*	Axial postgadolinium VIBE

*Optional for retrospective cohort.

DWI, diffusion-weighted imaging; HASTE, Half-Fourier Acquisition Single-shot Turbo spin Echo; TrueFISP, True Fast imaging with Steady State Precession; VIBE, volumetric interpolated breath-hold examination.

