##### Magnetic resonance Enterography Global Score (MEGS)

This score encompasses aspects of both inflammatory activity and bowel damage, and has been validated against several reference standards, including a composite clinical reference,^30^ faecal calprotectin^31^ and capsule endoscopy^32^ (table 2).

**Table 2 T2:** Calculation of Magnetic resonance Enterography Global Score (MEGS)

Mural features	0	1	2	3	Score
Mural thickness	<3 mm	>3–5 mm	>5–7 mm	>7 mm	a
Mural T2 signal (oedema)	Normal	Minor increase	Moderate increase	Large increase	b
Perimural T2 signal	Normal	Increased signal but no fluid	Small (≤2 mm) fluid rim	Large (>2 mm fluid rim)	c
Contrast enhancement: amount	Normal	Minor increase	Moderate increase	Large increase	d
Contrast enhancement: pattern	N/A or homogeneous	Mucosal	Layered		e
Haustral loss (colon only)	None	<1/3 segment	1/3–2/3 segment	>2/3 segment	f
Mural score for that segment					a+b+c+d+e+f =g
Multiplication factor	1	1.5	2	Total segmental score g * multiplication factor	
Length of disease in that segment	<5 cm	5–15 cm	>15 cm		

Each enteric segment (jejunum; proximal ileum; terminal ileum; caecum; ascending colon; transverse colon; descending colon; sigmoid colon; rectum) is scored separately. The segmental score is then multiplied by a factor depending on the length of disease involvement in that segment. Finally, scores for extramural features are added, giving a total score (maximum possible=296). Sum all segments, then add extramural score on a per-scan basis; five points for each of^1^: lymph nodes >1 cm short axis,^2^ comb sign (linear structures on the mesenteric border of an affected bowel segment),^3^ abscess and fistula^4^.

N/A, not applicable.

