##### Lémann Index (LI)

The LI^34^ (table 4) is based on comprehensive assessment of structural bowel damage, including stricturing, penetrating lesions (ﬁstulae and abscesses) and surgical resection, and is applicable to different settings, such as early or advanced disease, patients with or without surgery, or with different CD locations and extension. The score comprises several factors that can be assessed either clinically, or using imaging or via endoscopy. We will use the imaging-derived score. Since the anal canal will not have been imaged specifically for METRIC, we will omit this score.

**Table 4 T4:** Derivation of the Lémann Index

Organ	Method of assessment	N*	Segment	Grade 1	Grade 2	Grade 3
Surgical interventions†						
Upper tract	History	3	Oesophagus, stomach, duodenum	–	Bypass diversion or stricturoplasty	Resection
Small bowel	History	20	Each 20 cm SB segment	–	Bypass diversion or stricturoplasty	Resection
Colon/rectum	History	6	Each colonic segment	–	Stoma, bypass diversion or stricturoplasty	Resection
Stricturing lesions						
Upper tract	MRI	2	Stomach, duodenum	Wall <3 mm; segmental enhancement without prestenotic dilatation	Wall thickening ≥3 mm or mural stratification with no prestenotic dilatation	Stricture with prestenotic dilatation
Small bowel	MRI	20	Each 20 cm SB segment	Wall <3 mm; segmental enhancement without prestenotic dilatation	Wall thickening ≥3 mm or mural stratification with no prestenotic dilatation	Stricture with prestenotic dilatation
Colon/rectum	MRI	6	Each colonic segment	Wall <3 mm; segmental enhancement without prestenotic dilatation	Wall thickening ≥3 mm or mural stratification with no prestenotic dilatation	Stricture with prestenotic dilatation or >50% of the lumen
Penetrating lesions						
Upper tract	MRI	2	Stomach, duodenum	–	Deep transmural ulceration	Phlegmon or fistula
Small bowel	MRI	20	Each 20 cm SB segment	–	Deep transmural ulceration	Phlegmon or fistula
Colon/rectum	MRI	6	Each colonic segment	–	Transmural ulceration	Phlegmon or fistula

*n is the number of segments within a particular organ.

†This information will be collated from the original METRIC records, although a relevant surgical history will be very rare since included patients are, by definition, those with a new diagnosis of Crohn’s disease.

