### Sample size and justification

The sample size was based on including 207 participants newly diagnosed with CD. During the study, due to problems obtaining consent for additional follow-up hampered by COVID-19, the original target recruitment was necessarily reduced from 167 to 131 from the METRIC prospective cohort, and so an increased target of 76 participant retrospective cohort recruited from METRIC sites is anticipated. We anticipate this sample size will provide between 114 and 124 events (83–93 non-events). The number of the retrospective cohort will be increased to meet the 207 participant target if recruitment to the METRC cohort is below 131.

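### Table 1 lets retrospective scans omit contrast although the text exempts only DWI; MEGS as defined cannot be totalled without contrast, and one Lémann grade is lost

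*Protocol article*

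**What the plan says.** Three places in the protocol article bear on which retrospective scans are acceptable.

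- **MRI, Sequences (text).** Having described the METRIC minimum sequence set, the text says "This will also be required for retrospective accruals, excepting diffusion-weighted imaging (DWI"), and gives the reason that DWI is not needed for the activity and damage indices. No other exemption is stated.
- **MRI, Sequences (Table 1).** The asterisk that marks a sequence as optional for retrospective patients stands on the DWI row and also on the row "Coronal pregadolinium and postgadolinium VIBE (60–70s"). The latter is the only contrast sequence in the required column; the axial post-contrast sequence is optional for everyone.
- **Additional retrospective cohort: inclusion criteria.** The MRE must follow the METRIC minimum set. No contrast exemption is given.

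Two scoring tables refer to enhancement. Table 2 (MEGS) has an item "Contrast enhancement: amount" and a second item for enhancement pattern. Table 4 (Lémann Index) defines stricturing grade 1 as a wall under 3 mm with "segmental enhancement without prestenotic dilatation". Table 3 (sMaRIA) has no enhancement item.

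On numbers, Sample size and justification says "The sample size was based on including 207 participants newly diagnosed with CD". The METRIC target was "reduced from 167 to 131 from the METRIC prospective cohort", with "an increased target of 76 participant retrospective cohort recruited from METRIC sites is anticipated".

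**The concern.** A site or data manager cannot tell from the article whether an unenhanced retrospective scan is eligible. The text and the inclusion criteria say no; Table 1 says yes.

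The protocol's reason for waiving DWI does not carry over to contrast, because MEGS and part of the Lémann Index are built on enhancement. Both scores are in the primary comparison. If sites followed Table 1, MEGS could not be computed as defined on some scans, and the article does not say what the reader should then enter. The pattern item has a not-applicable level scored 0, but the amount item has none. Entering 0 for enhancement that was never imaged would lower MEGS in one cohort only and tie the predictor to the route of recruitment. Leaving such scans out would cost patients.

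**Working it through.** **1. The planned split reproduces.** 131 METRIC + 76 retrospective = 207. At the assumed 55–60% prevalence, events are 207 × 0.55 = 113.9 to 207 × 0.60 = 124.2, and non-events 207 × 0.40 = 82.8 to 207 × 0.45 = 93.2. These match the stated 114–124 and 83–93.

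**2. What each index loses without contrast.**

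| Index | Contrast-dependent part | Consequence |
|---|---|---|
| MEGS | Items d (0–3) and e (0–2) in every segment | Total as defined unavailable; other items scorable |
| Lémann | Stricturing grade 1 only | Grade 1 cannot be told from no lesion where the wall is under 3 mm |
| sMaRIA | None | Unaffected |

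In the Lémann table, grade 2 can be met by wall thickening, grade 3 by prestenotic dilatation, the penetrating grades do not name enhancement, and surgical items come from history.

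**3. Weight of the enhancement items in MEGS.** The maximum mural score per small-bowel segment is 3 + 3 + 3 + 3 + 2 = 14. Haustral loss adds 3 in the colon, giving 17. Enhancement contributes 3 + 2 = 5, so 5/14 = 36% and 5/17 = 29%. These are shares of the maximum score before the length multiplier. They do not estimate bias.

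**4. How many patients could be affected.** If the text rule was applied, none. If every planned retrospective scan lacked contrast, 76/207 = 36.7%. This is not a fixed ceiling, because "The number of the retrospective cohort will be increased to meet the 207 participant target" if METRIC recruitment falls short. With assumed METRIC totals of 120 and 100, the retrospective share would be 87/207 = 42% and 107/207 = 52%.

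**5. Complete-case illustration.** The unenhanced fractions below are assumptions, since the article gives none. Non-events are n × 0.40 to n × 0.45.

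| Unenhanced share of the 76 | Patients lost | Share of 207 | Patients left | Non-events left |
|---|---|---|---|---|
| 25% | 19 | 9% | 188 | 75–85 |
| 50% | 38 | 18% | 169 | 68–76 |
| 75% | 57 | 28% | 150 | 60–68 |
| 100% | 76 | 37% | 131 | 52–59 |

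The protocol's benchmark is 80–100 events, and its Assumptions section lets the smaller outcome group set the requirement. At 60% prevalence, losing 8 scans takes non-events below 80 (199 × 0.40 = 79.6). At 55% it takes 30 scans (177 × 0.45 = 79.7). This shows what exclusion would cost; the protocol does not plan exclusion.

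**The case against.** The strongest reply is that the text and the inclusion criteria agree, so the asterisk is a slip and few or no unenhanced scans were accepted. That may be so, and nothing in the article shows otherwise. The published table would still be wrong on eligibility, and only a count of unenhanced scans can settle whether any site relied on it.

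A second reply is that multiple imputation is already planned for missing covariates, and the MRE scores are covariates. This largely stands. Missingness that depends only on cohort, an observed variable, is compatible with missing at random once cohort is in the imputation model. What remains open is whether an unscorable enhancement item counts as missing or as 0; the MEGS table invites the second reading for the pattern item.

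Three stronger readings are tempting and not supported:

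- A reader might infer that MEGS is unavailable for 37% of patients. That needs all 76 scans to be unenhanced, and the article gives no count.
- A reader might infer that two of the three scores cannot be calculated. The Lémann Index is degraded at one grade and remains calculable.
- A reader might infer that the primary analysis falls to 131 patients. The stated method is imputation, so complete-case loss is not what the protocol plans.

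Finally, closure was expected in late 2022 or early 2023, so correcting the footnote will not change scans already collected. That is why an analysis rule is needed as well.

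**Conclusion.** The contradiction is certain: Table 1 makes contrast optional for retrospective patients, while the text exempts only DWI and the inclusion criteria require the minimum set. It matters chiefly for MEGS, whose total as defined cannot be formed without items d and e. For the Lémann Index the effect is confined to stricturing grade 1, and sMaRIA is untouched.

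The size of the effect is unknown. It ranges from no patients, if the text was followed, to 76 of 207 (37%) under the planned split, and higher if the retrospective cohort grew. Scoring absent enhancement as 0 is a risk left open by the article; nothing in it says this will be done.

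**What to change.** 1. Reconcile Table 1 with the Sequences text and the retrospective inclusion criteria. Because the reason given for exempting DWI does not hold for contrast, the asterisk on the gadolinium row appears to be the error.
2. Report how many retrospective scans lack contrast.
3. For any already accrued, set the enhancement-dependent MEGS and Lémann items to missing, never to zero.
4. Include cohort in the multiple imputation already planned. This separates cohort from enhancement only if some retrospective scans are enhanced. If none are, the imputation assumes that enhancement relates to the other items in the same way in both cohorts, and the report should say so.
5. Repeat the MEGS and Lémann comparisons in contrast-enhanced scans only, as a sensitivity analysis.

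The cost is one table footnote, one scoring rule and one extra sensitivity analysis. A few retrospective candidates may need to be replaced.

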#### MRE activity scores

We will calculate established MRE activity indices as follows.

##### Magnetic resonance Enterography Global Score (MEGS)

This score encompasses aspects of both inflammatory activity and bowel damage, and has been validated against several reference standards, including a composite clinical reference,^30^ faecal calprotectin^31^ and capsule endoscopy^32^ (table 2).

**Table 2 T2:** Calculation of Magnetic resonance Enterography Global Score (MEGS)

Mural features	0	1	2	3	Score
Mural thickness	<3 mm	>3–5 mm	>5–7 mm	>7 mm	a
Mural T2 signal (oedema)	Normal	Minor increase	Moderate increase	Large increase	b
Perimural T2 signal	Normal	Increased signal but no fluid	Small (≤2 mm) fluid rim	Large (>2 mm fluid rim)	c
Contrast enhancement: amount	Normal	Minor increase	Moderate increase	Large increase	d
Contrast enhancement: pattern	N/A or homogeneous	Mucosal	Layered		e
Haustral loss (colon only)	None	<1/3 segment	1/3–2/3 segment	>2/3 segment	f
Mural score for that segment					a+b+c+d+e+f =g
Multiplication factor	1	1.5	2	Total segmental score g * multiplication factor	
Length of disease in that segment	<5 cm	5–15 cm	>15 cm		

Each enteric segment (jejunum; proximal ileum; terminal ileum; caecum; ascending colon; transverse colon; descending colon; sigmoid colon; rectum) is scored separately. The segmental score is then multiplied by a factor depending on the length of disease involvement in that segment. Finally, scores for extramural features are added, giving a total score (maximum possible=296). Sum all segments, then add extramural score on a per-scan basis; five points for each of^1^: lymph nodes >1 cm short axis,^2^ comb sign (linear structures on the mesenteric border of an affected bowel segment),^3^ abscess and fistula^4^.

N/A, not applicable.

##### Simplified Magnetic Resonance Index of Activity (sMaRIA)

The simplified MAgnetic Resonance Index of Activity (sMaRIA) has been validated against endoscopic reference standards, and is used increasingly to assess treatment response in clinical trials^8 10–12 33^ (table 3).

**Table 3 T3:** Derivation of the simplified MAgnetic Resonance Index of Activity (sMaRIA)

Feature	Description
Mural thickness	Binary: measured in mm using software callipers, scored as abnormal if >3 mm
Mural oedema	Binary: present if there is high signal intensity on T2 sequences with fat saturation, compared with normal-appearing loops
Fat stranding	Binary: present if there is loss of the normal sharp interface between the intestinal wall and mesentery, with oedema/fluid in the perienteric fat
Ulceration	Binary: present if mucosal surface has a deep depression, visible on 2 MRI sequences
sMaRIA score for that segment	=1 point for each of mural thickness, mural oedema and fat stranding; 2 points for ulceration (maximum 5 points per segment)

##### Lémann Index (LI)

The LI^34^ (table 4) is based on comprehensive assessment of structural bowel damage, including stricturing, penetrating lesions (ﬁstulae and abscesses) and surgical resection, and is applicable to different settings, such as early or advanced disease, patients with or without surgery, or with different CD locations and extension. The score comprises several factors that can be assessed either clinically, or using imaging or via endoscopy. We will use the imaging-derived score. Since the anal canal will not have been imaged specifically for METRIC, we will omit this score.

**Table 4 T4:** Derivation of the Lémann Index

Organ	Method of assessment	N*	Segment	Grade 1	Grade 2	Grade 3
Surgical interventions†						
Upper tract	History	3	Oesophagus, stomach, duodenum	–	Bypass diversion or stricturoplasty	Resection
Small bowel	History	20	Each 20 cm SB segment	–	Bypass diversion or stricturoplasty	Resection
Colon/rectum	History	6	Each colonic segment	–	Stoma, bypass diversion or stricturoplasty	Resection
Stricturing lesions						
Upper tract	MRI	2	Stomach, duodenum	Wall <3 mm; segmental enhancement without prestenotic dilatation	Wall thickening ≥3 mm or mural stratification with no prestenotic dilatation	Stricture with prestenotic dilatation
Small bowel	MRI	20	Each 20 cm SB segment	Wall <3 mm; segmental enhancement without prestenotic dilatation	Wall thickening ≥3 mm or mural stratification with no prestenotic dilatation	Stricture with prestenotic dilatation
Colon/rectum	MRI	6	Each colonic segment	Wall <3 mm; segmental enhancement without prestenotic dilatation	Wall thickening ≥3 mm or mural stratification with no prestenotic dilatation	Stricture with prestenotic dilatation or >50% of the lumen
Penetrating lesions						
Upper tract	MRI	2	Stomach, duodenum	–	Deep transmural ulceration	Phlegmon or fistula
Small bowel	MRI	20	Each 20 cm SB segment	–	Deep transmural ulceration	Phlegmon or fistula
Colon/rectum	MRI	6	Each colonic segment	–	Transmural ulceration	Phlegmon or fistula

*n is the number of segments within a particular organ.

†This information will be collated from the original METRIC records, although a relevant surgical history will be very rare since included patients are, by definition, those with a new diagnosis of Crohn’s disease.

#### Interpretation and blinding

MRE scans will be interpreted by one from a pool of recruitment site radiologists; all are GI radiologists and experienced in MRE, in both clinical and research settings. Radiologists will be allocated MRE scans for scoring. These will be interpreted blinded to all clinical information other than that relevant for the calculation of the relevant index (eg, surgical history for LI).

#### Ultrasound

The arm from the METRIC trial will not be considered.

### Assessment of disease severity at follow-up

#### Time point of follow-up

Follow-up will be for a minimum of 4 years: since participants were recruited to METRIC over 30 months, this corresponds to an average follow-up of approximately 5.5 years. This provides sufficient time for clinically relevant complications of CD to manifest.^35–37^

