#### Additional retrospective cohort: inclusion criteria

The retrospective cohort will be added to METRIC accruals to achieve the required sample size.

Inclusion criteria for the retrospective cohort are as follows:

Patients aged 16 years or more with newly diagnosed CD, based on endoscopic, histological, clinical and radiological findings.MRE acquired according to METRIC standard minimum sequence data set, and performed either <3 months before or after diagnosis.Normal institutional practice is to perform MRE in all new diagnoses of CD.At least 4 years clinical follow-up data available.

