### Outcomes

#### Primary outcome

Comparative predictive ability of prognostic models incorporating MRE severity scores (MEGS, sMaRIA and Lémann index) versus models using standard characteristics alone to predict disabling CD (modified Beaugerie definition) within 5 years of new diagnosis.

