#### Secondary outcomes

##### Secondary outcome 1

Comparative predictive ability of models incorporating MRI severity scores (MEGS, sMaRIA and LI) when compared with a baseline model of standard characteristics alone, for predicting Montreal B2/B3 disease or Liège severe disease in newly diagnosed patients by 5 years.

Modelling will be conducted as for the primary outcome. Models will only be developed if the number of events/non-events is adequate; if this is not achieved, only descriptive statistics will be provided.

##### Secondary outcome 2

Identification of the best combination of individual MRE features for prediction of disabling CD (all definitions) within 5 years of new diagnosis. PCA will be used to combine multiple MRE parameters into a small number of Eigenscore variables. This allows a larger number of features to be combined without compromising statistical power. The most influential imaging features will be identified for further simplification of MRE variables included in modelling. Methods will be as in the primary outcome, and the statistical significance of including MRE features will be evaluated based on improvement of model fit (BIC) in comparison to the standard model, with additional model performance reported as appropriate.

##### Secondary outcome 3

Average per-patient and national healthcare cumulative costs incurred within 5 years of newly diagnosed CD. Hospital healthcare usage from health economic case report forms (CRFs) will be multiplied by unit costs for relevant items, summed across the 5-year follow-up period, and averaged across the study population (median and mean). Mean costs per patient will be multiplied by the estimated number of CD patients in the UK, stratifying by the presence or absence of disabling disease, to estimate the cost-of-illness following a UK diagnosis (both by UK incidence and prevalence).

##### Secondary outcome 4

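### The outcome is status within 5 years but follow-up is assured only to 4, so the planned 83–93 non-events are not all verified, and retrospective entry depends on later retention

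*Protocol article*

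**What the plan says.** The primary outcome (Outcomes, Primary outcome) compares models with MRE scores against "models using standard characteristics alone to predict disabling CD (modified Beaugerie definition) within 5 years of new diagnosis". One component of the modified Beaugerie definition counts corticosteroid courses over 5 years.

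On follow-up, Time point of follow-up states: "Follow-up will be for a minimum of 4 years: since participants were recruited to METRIC over 30 months", and adds that "this corresponds to an average follow-up of approximately 5.5 years". For the retrospective cohort, the inclusion criteria require: "At least 4 years clinical follow-up data available".

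Under Sample size and justification, "the original target recruitment was necessarily reduced from 167 to 131 from the METRIC prospective cohort", and "an increased target of 76 participant retrospective cohort recruited from METRIC sites is anticipated". That gives 131 + 76 = 207. The Assumptions section expects 114–124 events and 83–93 non-events from these 207 and says the smaller group determines the minimum sample size.

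Under Statistical methods, better performance means more patients correctly classified, measured by sensitivity, specificity and net benefit. BIC, a c-index and predictions at 1, 2 and 3 years are also reported. Multiple imputation is stated for covariates. The consensus panels record the date on which the endpoint was reached. Costs under Secondary outcome 3 are "summed across the 5-year follow-up period, and averaged across the study population".

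**The concern.** A patient last seen event-free at 4.3 years has no known 5-year status. The article sets a 5-year outcome, assures 4 years of observation, and then counts non-events as though every patient were classified at 5 years. Three stated elements are affected whatever a separate analysis plan contains:

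- The non-event count that justifies the sample size presumes complete 5-year status.
- Sensitivity, specificity, net benefit and the number correctly classified need either known 5-year status or a method that allows for censoring.
- The retrospective entry rule conditions on something that happens after baseline. Patients who move away, leave hospital care or die before 4 years without the required data never enter, and no analysis of those who did can recover them. Contact with the general practitioner (Retention) is limited to METRIC patients and consented retrospective patients, whereas retrospective data may be collected without direct consent.

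At stake are the absolute 5-year risk, specificity and net benefit, and the 5-year cost estimate.

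**Working it through.** **The plan's own count.** 207 × 0.55 = 113.9 and 207 × 0.60 = 124.2 events; 207 × 0.45 = 93.2 and 207 × 0.40 = 82.8 non-events. These match the stated 114–124 and 83–93, and they use all 207 as classified at 5 years.

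**METRIC patients with under 5 years (share f).** Recruitment over 30 months with a 4-year minimum gives follow-up of 4.0 to 6.5 years. Accrual dates are not given, so two patterns were assumed.
- Uniform accrual: f = 12/30 = 40%, or 131 × 0.40 = 52 patients. Mean follow-up is 4 + 2.5/2 = 5.25 years.
- Front-loaded accrual matched to the stated 5.5-year mean (follow-up = 4 + 2.5U, U ~ Beta(1.5, 1), mean U = 0.6): f = 0.4^1.5 = 25.3%, or 33 patients.
- METRIC allows diagnosis up to 3 months before recruitment. If every patient had that full lag under uniform accrual, f = 9/30 = 30% and the mean is 5.5 years, inside the same range.

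**Non-events verified at 5 years.** Let S5 be the event-free proportion at 5 years and q the share of retrospective patients with at least 5 years (not given, so ranged from 0 to 1):

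verified = S5 × [131 × (1 − f) + 76 × q]

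With 57% disabling by 5 years (S5 = 0.43; 89 non-events in all):

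| f | q = 1 | q = 1 − f | q = 0 |
|---|---|---|---|
| 40% | 66.5 | 53.4 | 33.8 |
| 25.3% | 74.8 | 66.5 | 42.1 |

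Over the protocol's 55–60% range, the lowest value is 0.40 × 78.6 = 31.4 and the highest 0.45 × (97.9 + 76) = 78.2. The stated counts at those same prevalences are 83 and 93.

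**Later events mislabelled if patients event-free at 4–5 years were classed as non-events.** This is the number with short follow-up times the fall in event-free proportion from last contact to 5 years. Constant hazard and linear accrual were both used, because the article states linear accrual while its 58% extrapolation is reproduced by a constant hazard: 1 − 0.84^5 = 58%.
- Smallest: 55%, constant hazard, f = 25.3%, all retrospective patients reaching 5 years. Mean follow-up of the 33.1 short METRIC patients is 4.6 years. S(4.6) = 0.45^0.92 = 0.480, so 33.1 × 0.030 = 1.0.
- Largest: 60%, linear, f = 40%, all retrospective patients stopping at exactly 4 years. METRIC: 52.4 × (0.46 − 0.40) = 3.1. Retrospective: 76 × (0.52 − 0.40) = 9.1. Total 12.3.

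At the largest, absolute risk would be understated by 12.3/207 = 5.9 percentage points, and 12.3/(82.8 + 12.3) = 13% of the nominal non-events would really be events.

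**Costs, with level spending and no adjustment.** Uniform accrual, only METRIC patients short by a mean of 0.5 year: (52.4 × 0.5/5)/207 = 2.5%. With all 76 retrospective patients also short by 1 year: (5.24 + 76 × 1/5)/207 = 9.9%. Under the front-loaded pattern the lower end is (33.1 × 0.4/5)/207 = 1.3%.

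**The case against.** **Censoring may already be handled.** The article does not name the model type. Recorded endpoint dates, a c-index and 1-, 2- and 3-year horizons all fit a survival analysis, and censoring rules are commonly left to an analysis plan. This stands. A reader might infer that patients event-free at 4–5 years are to be counted as non-events, or that costs will ignore short follow-up, but no section says so. The mislabelling and cost figures are therefore conditional.

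**The 31–78 are complete cases.** In a time-to-event model censored patients still contribute, and the 80–100 benchmark is worded as events. This also stands: the figures do not show that the study is too small. Nor is it fair to set 207 × (1 − 0.84^4) = 104 events against the stated 114–124, because that stops every patient at exactly 4 years.

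**Mean follow-up.** It is tempting to call 5.5 years an error for 5.25. That needs uniform accrual and a cut-off exactly at the minimum, and it ignores diagnosis before recruitment. Trial status reports delay, so actual follow-up may exceed the minimum.

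**Direction of selection.** One might suppose that leavers are milder and that the entry rule inflates event risk. The article gives no leaving rates, so the direction is unknown.

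**The outcome is comparative.** Both models are judged in the same patients, and a few late events may not change which performs better. That is fair, but sensitivity, specificity, net benefit and costs are reported in absolute terms.

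What remains is the stated non-event count, which presumes status the design does not assure, and an entry rule that analysis cannot undo.

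**Conclusion.** The concern holds in a limited form. The 5-year outcome, the 4-year assurance and the non-event count do not fit together. Verified 5-year non-events would be about 31–78 against the stated 83–93, assuming 55–60% prevalence, 25–40% of METRIC patients under 5 years, follow-up ending at the stated minimum, and any share of retrospective patients reaching 5 years. Loss of verified status is the larger effect: about 14–27 METRIC patients would be event-free with unknown 5-year status, rising to about 51–69 of 207 if every retrospective patient stopped at 4 years. Mislabelled events would be about 1–12, and only if such patients were classed as non-events. Selection on retention affects 76 of 207 patients (37%); it can bias that cohort, with direction and size unknown. This should be settled before analysis, because it touches both the primary outcome and the sample-size justification.

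**What to change.** 1. Fit a time-to-event model using the endpoint date the panels already record. Censor at last follow-up and truncate at 5 years. Estimate 5-year sensitivity, specificity and net benefit with Kaplan-Meier or inverse-probability-of-censoring weighting. If the analysis plan already does this, say so in the protocol.
2. Replace the retrospective criterion of 4 years of available data with a calendar rule: consecutive new diagnoses with an eligible MRE at least 4 years before data cut-off, whatever their retention. Censor those who leave.
3. Restate the counts in Assumptions, giving the number with verified 5-year status separately from the number censored.
4. Estimate 5-year costs with a method that allows for censoring.
5. Report the actual distribution of follow-up from diagnosis, by cohort. The stated mean need not be replaced by another assumed figure.

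The cost is analysis wording, a small amendment to one criterion and slightly wider intervals. The 207-patient target need not change for the estimates to be valid.
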